### Statistical analysis

The primary objective of the STEP study is to examine the effects of short bouts of structured PA to increase preschool-age children’s total school-day PA, as well as percent time spent in MVPA during the school day. The preschool center is the unit of randomization and intervention; the individual child is the unit of measurement. The analyses will use the child-level data, accounting for correlation of child responses within class and of classrooms within a center. For all analyses of primary outcomes and mediating variables we will use generalized linear modeling statistical methods. The methods allow assessment of a simple treatment comparison as well as multivariable modeling. Mediator and modifier significance (set *a priori* at a significance level of 0.25 or below) will be assessed univariately to determine which variables will be eligible for inclusion in the multivariable model. Intervention effects (change in PA) will be assessed with repeated measures mixed model analysis of variance or covariance, with childcare center as a random effect given that we do not expect that the within-group time trends will be homogeneous. Using a mixed effects model allows us to incorporate random effects for the center and class within center (clusters) and thereby model the correct covariance structure of the data and produce more accurate estimates of the effects under study and their standard errors. The distributions of individual variables will be evaluated and the data transformed as necessary to meet the assumptions of normality and homoskedasticity. For categorically scaled measures, we will use the generalized estimating equation methods for logistic regression analysis. Demographic variables will be added to multivariate models along with potential interactions with the intervention. Significant (at the p = 0.05 level) variables and interactions will be retained in the final model. For the baseline characteristics statistical comparison between groups was made with Wilcox Rank Sum tests for scaled variables and Chi-Square tests for categorical variables, with a two-sided alpha = 0.05. All analyses will be computed using SAS (version 9.2).

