#### Sample size and power calculations

Sample size was determined using methods for studies with randomization by cluster [32]. With 25 children per preschool center and five preschool centers per condition, we have 80% power to detect a significant difference in the mean change in number of minutes of PA (2-sided) between the two conditions of between 5.5 and 10.7 min of total school day PA at the 5% significance level, depending on the correlation ranges above. Thus we have adequate power to detect a difference that would be significant both statistically and clinically. Based on the assumption that repeat measures of PA within clusters will only be moderately related after adjusting for repeat measures at the individual level, this power will hold similarly when analyzing the full (3 observation points) study using a random coefficients model [33].

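### The random effects named for the intervention analysis do not, as intercepts, model the differing time trends given as their reason, and the two statistical sections do not fix one model

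*Protocol article*

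**What the plan says.** Three statements in the Protocol article bear on this.

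- Statistical analysis, the effect of interest: "Intervention effects (change in PA) will be assessed with repeated measures mixed model analysis of variance or covariance". The center effect is then introduced "with childcare center as a random effect given that we do not expect that the within-group time trends will be homogeneous".
- Statistical analysis, the random effects: the mixed model is said to "incorporate random effects for the center and class within center (clusters) and thereby model the correct covariance structure of the data". No center-by-time term, class-by-time term or random slope is named.
- Sample size and power calculations: power is stated for a difference in mean change between conditions, and "this power will hold similarly when analyzing the full (3 observation points) study using a random coefficients model". The level of the random coefficients (child, class or center) is not given.

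On the design, the Statistical analysis section says: "The preschool center is the unit of randomization and intervention; the individual child is the unit of measurement". PA is measured at baseline, 3 months and 6 months.

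**The concern.** With PA measured at three visits, an intervention effect on change is a condition-by-time effect. A random center intercept raises or lowers all of a center's visits by the same amount, and a class intercept does the same for a class. Both drop out when one visit is subtracted from another. Such terms handle differences in level between centers. They do not handle centers drifting apart over time, which is the reason the article gives for including the center effect.

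Drift shared by a center's children (season, staff, play space) is then treated as independent information from each child. With only 10 randomized centers, the standard error of the treatment effect on change would be too small and the primary test too liberal. A random coefficients model with center-level slopes would prevent this. One with child-level slopes alone would not, and the article does not say which is meant.

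**Working it through.** **1. The plan's own figure.** The power section gives a detectable difference of 5.5 to 10.7 min at 80% power and two-sided 5%: "With 25 children per preschool center and five preschool centers per condition", that is 125 children per arm. Neither the SD of change nor the ICC is given, and the correlation ranges that the sentence refers to do not appear in the article. The figure can therefore only be solved backwards:

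- Detectable difference = (1.96 + 0.84) × SD × √(2 × DEFF / 125), with DEFF = 1 + 24 × ICC.
- 5.5 min implies SD × √DEFF = 15.5 min; 10.7 min implies 30.2 min.
- Variance ratio = (10.7 / 5.5)² = 3.78. If the SD is fixed, the whole range comes from clustering and the lower end is ICC 0, the upper end is ICC = (3.78 − 1) / 24 = 0.116.

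This neither confirms nor refutes the stated figure. It shows only that, under those conditions, ICCs up to 0.10 lie inside the plan's own range.

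**2. Why an intercept cancels.** Write PA for child i in center j at visit t as: fixed part(t) + c(j) + child and residual terms. The change from visit 0 to visit t contains c(j) − c(j) = 0. A class intercept cancels in the same way. If the center term varies by visit, c(j,t), the change contains c(j,t) − c(j,0), which every child in the center shares and which a constant c(j) does not represent.

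**3. Is such variation expected?** The Statistical analysis section expects trends that are not homogeneous. The power section assumes that repeat measurements within clusters are only moderately related once individual-level repetition is allowed for. An intercept alone would make the center component perfectly correlated across visits. Both statements point to center-by-time variance above zero, but neither gives its size.

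**4. Size if it is left out.** Let ρ be the ICC of the change score (assumed), with m = 25 children per center. This takes within-child correlation as correctly modelled and omits any class-level variation in change.

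- DEFF = 1 + 24ρ
- Type I error = 2 × (1 − Φ(1.96 / √DEFF))
- SE understated by 1 − 1/√DEFF

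| ρ (assumed) | DEFF | Type I error, formula | Type I error, simulated | SE understated by |
|---|---|---|---|---|
| 0 | 1.00 | 0.050 | 0.049 | 0% |
| 0.005 | 1.12 | 0.064 | 0.065 | 6% |
| 0.01 | 1.24 | 0.078 | 0.077 | 10% |
| 0.02 | 1.48 | 0.107 | 0.111 | 18% |
| 0.05 | 2.20 | 0.186 | 0.183 | 33% |
| 0.10 | 3.40 | 0.288 | 0.297 | 46% |

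The simulation used 20,000 sets of change scores per ρ, with 5 centers of 25 children per arm. On the same data, a test of center means on 10 − 2 = 8 df rejected 0.047 to 0.052 of the time at every ρ.

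A small set of three-visit mixed-model fits at ρ of about 0.05 pointed the same way: 0.219 with random intercepts only, and 0.036 with a center slope and 8 df. There were only 192 runs, with Monte Carlo standard errors of about 0.03 and 0.013 and many convergence warnings, so these fits are supporting evidence only.

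**The case against.** The strongest reply is that the article can be read in ways that remove the problem.

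- It never uses the word intercept. Its only reason for the center effect is differing time trends, and the power section names a random coefficients model, which ordinarily means random time slopes. Read together, the sections could describe a model with center-level slopes.
- Analysis of variance or covariance for change could mean a model for change scores, or for follow-up adjusted for baseline. A random center effect there does capture center-level variation in change. The power statement, "80% power to detect a significant difference in the mean change in number of minutes of PA (2-sided) between the two conditions", fits that reading.
- No denominator degrees of freedom are stated. A reader might infer that the effect will be tested against child-level error on hundreds of degrees of freedom, but the article does not say so. Such detail is commonly left to an analysis plan, which is not shown, so its absence is not a fault.
- The ICCs of change are assumed, and at very small values the inflation is slight.

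All four points stand, and they limit the claim. They do not remove it. The listed terms, read as they are usually fitted to repeated measurements, do not do the job stated for them. The random coefficients phrase does not help until its level is given, because child-level slopes alone would leave center-level drift unmodelled.

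**Conclusion.** The concern holds as a mismatch and an ambiguity in what the article states. The reason given for the center effect calls for a term that varies over time, the terms named do not include one, and the two statistical sections do not fix a single model. On the literal intercept reading, the condition-by-time test is too liberal by the amounts tabulated. Those amounts rest on an assumed ICC of change, 25 children in each of 10 centers, and a correctly modelled within-child correlation.

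A reader might go further and conclude that the trial's error rate is inflated, or that a false positive is likely. The documents do not support either statement. The model may in fact include center-level change, no ICC is reported, and even the highest assumed value gives a rejection rate of 29% under a true null.

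**What to change.** State one model and use it in both the Statistical analysis and the Sample size and power calculations sections. Either of two forms would serve:

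- a repeated measures model with a center-level random time slope or a center-by-time random effect, a class-by-time effect where it can be estimated, and a within-child covariance structure; or
- a random center effect in a model for change, or for follow-up adjusted for baseline.

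In either form, test the intervention effect with center-based denominator degrees of freedom, about 8 for 10 centers in two arms, for example by Kenward-Roger. If the random coefficients model is kept as the name, say that the coefficients vary by center.

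The cost is a few lines of wording and model code, and wider confidence intervals when centers differ in change. With 10 centers and 34 classrooms the class-by-time term may not converge, so the text should say in advance that this term is dropped first and that the center-level term stays.

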### Participant recruitment and eligibility

A total of 15 preschool centers with a minimum of two full-day classrooms that serve low-SES areas in Springfield, Massachusetts area were approached to participate in STEP. Ten of the 15 preschool centers approached met the screening criteria and agreed to participate in the study. Reasons preschool centers declined participation included unwillingness to be randomized and inability to consistently provide 30 min of morning and afternoon gross-motor playtime per preschool day. Although not a requirement for eligibility, we assessed the existing PA policies for each of the 10 preschool centers enrolled in the study for randomization/stratification purposes. Existing PA policies were assessed using a modified version of the Environment and Policy Assessment and Observation Audit Tool (EPAO)[10]. The assessment included written PA policy, teacher training in PA and involvements with children during gross-motor playtime, and indoor and outdoor PA equipment.

Within each preschool center, between 25 – 30 children were individually recruited for the assessment portion of the study. Children were eligible for the assessment portion of the study if they: 1) attended one of the 10 participating preschool centers; 2) were between 2.9 – 5 years of age on the date of baseline assessment; 3) did not have a condition limiting their participation in MVPA (e.g., unable to participate in routine gross-motor playtime at preschool); 4) unable to wear the activity monitor, and 5) attend preschool full-time. Children that were excluded due to eligibility criteria or whose parents did not wish to sign the informed consent were still allowed to participate in the intervention protocol; however no assessment data were collected on them.

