## Results

This study is ongoing. We successfully recruited five preschool centers per treatment group (total of 10 preschool centers, 34 classrooms). A total of 680 students from all preschool centers were eligible to participate in the study. Of those, 331 families responded to our advertisement and were eligible for participation. Prior to the initiation of the study, 16 participants were terminated from the preschools, for a total of 315 children enrolled at baseline. Baseline assessment was completed by 92% of eligible families. Baseline variables did not significantly differ between preschool centers for each group (SBS-PA and UPA); therefore their data were combined for this report. Baseline socio-demographic characteristics are presented in Table 1. The study population consisted of 50.2% boys and 49.8% girls. The majority of the participants were either African-American (25%) or Latino/Hispanic (41%). The racial/ethnic composition of the participants is representative of the 10 preschool centers student population. Fifty-four percent of the study population was from single-parent homes and 59% of the study sample had annual household incomes less than $40,000.

**Table 1 T1:** Baseline demographic characteristics

**Variable**	**SBS-PA**	**UPA**	**p**	**All**
	**(n = 141)**	**(n = 150)**		**(n = 291)**
Gender, n (%)				
Boys	59 (52%)	62 (49%)	0.65	121 (50.2%)
Girls	55 (48%)	65 (51%)		120 (49.8%)
Race/Ethnicity, n (%)				
White	36 (34%)	36 (29%)	0.13	72 (31%)
Hispanic	35 (33%)	59 (48%)		94 (41%)
African-American	33 (31%)	25 (20%)		58 (25%)
Asian	2 (2%)	3 (2%)		5 (2%)
Other	0 (0%)	1 (1%)		1 (0.4%)
Parent/guardian age (yrs)	43.8 ± 7.7	44.0 ± 7.6	0.73	43.9 ± 7.6
Parent/guardian BMI (kg/m^2^)	27.8 ± 6.1	27.4 ± 6.0	0.43	27.6 ± 6.0
Parent/guardian marital status, n (%)				
Married	51 (45%)	57 (45%)	0.27	108 (45%)
Divorced/Separated or widowed	12 (10%)	6 (5%)		18 (7%)
Single-never married	51 (45%)	63 (50%)		114 (47%)
Maximum household education level, n (%)				
High school graduate or less	31 (32%)	44 (36%)	0.64	75 (34%)
Some college/technical school	24 (24%)	32 (26%)		56 (25%)
College graduate	43 (44%)	46 (38%)		89 (40%)
Annual total household income, n (%)				
Less than $20,000	28 (26%)	34 (29%)	0.57	62 (27%)
$20,000 - $39,000	32 (29%)	40 (34%)		72 (32%)
$40,000 - $59,000	13 (12%)	15 (13%)		28 (12%)
Greater than $60,000	36 (33%)	29 (25%)		65 (29%)

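### Logistic GEE with ten randomised centers: in its usual uncorrected form, a nominal 5% test of a categorical measure has a true error of about 11–14%

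*Protocol article*

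**What the plan says.** In the Statistical analysis section, effects on physical activity go to a repeated-measures mixed model with random effects for center and for class within center. Categorical measures get a different method: "For categorically scaled measures, we will use the generalized estimating equation methods for logistic regression analysis". The article gives no working correlation, cluster level, variance estimator, reference distribution or small-sample adjustment for that method.

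The same section fixes the randomised unit: "The preschool center is the unit of randomization and intervention; the individual child is the unit of measurement". It also says that the analyses will account for correlation of children within a class and of classes within a center.

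The number of randomised units is small. The power section plans on it ("With 25 children per preschool center and five preschool centers per condition") and the Results section confirms it: "We successfully recruited five preschool centers per treatment group (total of 10 preschool centers, 34 classrooms").

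**The concern.** The robust (sandwich) variance that normally accompanies GEE is justified by a large number of clusters, not a large number of children. With five centers per arm, two things go wrong in the same direction. The sandwich variance is biased downward, because each arm's mean is estimated from the same few center residuals that are then used to estimate its variance. In addition, the Wald z test compares a statistic with about 8 degrees of freedom to a normal distribution.

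If the analysis is run that way, effects on categorical measures would be called significant too often and their confidence intervals would be too short. The mixed models for the continuous outcomes carry center as a random effect. The article states no comparable safeguard for the GEE.

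**Working it through.** **The plan's own figure.** The article gives no error rate for the GEE test. Its only design figure is a detectable difference of 5.5 to 10.7 minutes at 80% power, two-sided 5%, which concerns continuous activity minutes. It cannot be reproduced from the text, because neither a standard deviation nor an intracluster correlation (ICC) is given. It has no bearing on what follows.

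**Inputs from the article**
- k = 5 centers per arm, 10 in all (power section, Results).
- 25 children per center (power section); recruitment target 25–30 (Participant recruitment and eligibility).
- Two-sided 5% level. This is stated for the power calculation and assumed here for the categorical tests.
- An illustrative proportion of 0.35, the approximate share overweight or obese (Discussion and Conclusions).

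**Assumptions**
- ICC from 0 to 0.10.
- Proportions of 0.15 and 0.50 as well as 0.35.
- Usual form of GEE: clustered on center, uncorrected robust standard error, Wald z.

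**Step 1, direct calculation.** Take equal center sizes and no covariates. For one arm with center proportions p_j and mean p̄:
- sandwich variance of p̄ = Σ(p_j − p̄)² / k²
- unbiased variance of p̄ = Σ(p_j − p̄)² / [k(k − 1)]
- ratio = (k − 1)/k = 4/5

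The robust z statistic is therefore the two-sample t statistic on center proportions, with 2(k − 1) = 8 df, multiplied by √(5/4). The test rejects when |t8| > 1.96 × √(4/5) = 1.753:
- true error = 2 × P(t8 > 1.753) = **0.118**

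The number of children per center does not enter. Of the two faults, the normal reference alone (unbiased variance, z cut-off) gives 2 × P(t8 > 1.96) = 0.086. The variance bias takes it from there to 0.118.

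**Step 2, interval width.** A correct interval uses the 97.5% point of t8, which is 2.306. The ratio of the usual half-width to the correct one is 1.753 / 2.306 = 0.76, so the usual interval is about 24% too short.

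**Step 3, simulation under no effect.** The first two rows use beta-binomial data, 15,000 trials per scenario and an independence working correlation. The third uses a fitted exchangeable GEE with 1,500 trials per scenario.

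| Setting (uncorrected robust Wald z, clustered on center) | Type I error |
|---|---|
| Equal centers of 25; proportion 0.15–0.50; ICC 0–0.10 | 0.112–0.128 |
| Unequal centers (15–44); same grid | 0.118–0.138 |
| Exchangeable GEE, proportion 0.35, ICC 0.02 and 0.05 | 0.111–0.112 |

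The result changes little with the assumed ICC or proportion. Adding two center-level covariates to the exchangeable GEE (about 1,200 trials) raised the error to about 0.21–0.22. The article does not say that the GEE will include such covariates, so this shows sensitivity only.

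**Step 4, other GEE tests on the same beta-binomial scenarios**

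| Test | Type I error |
|---|---|
| Uncorrected robust SE, t8 reference | 6.7–8.8% |
| Robust score test | 5.0–6.0% |
| Milder leverage correction, residuals × 1/√(1 − h), t8 | 4.6–5.8% |
| Stronger leverage correction, residuals × 1/(1 − h), t8 | 2.9–3.5% |

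**The case against.** The strongest reply is that the faulty test is assumed, not written. The article names GEE only. A robust score test, or a corrected variance with t8, is also a GEE analysis and holds its level near or below 5%. An article commonly leaves the variance estimator to the full plan, which may contain a correction. This stands to the extent that the 11–14% must be conditional. It does not dispose of the point: the article commits to a method whose ordinary form fails with this number of centers.

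Three stronger readings are tempting, and the article supports none of them.
- **That the trial's main result is at risk.** The outcomes under General design (whole-day activity, share of time in MVPA, sedentary time) are continuous, and effects on activity go to the mixed model. No categorical measure is named as an outcome. Observed activity level is recorded as a code, but Table 2 summarises it as a percentage of intervals, so it may not reach the GEE at all. Location, initiator and group composition are described as context for the activity.
- **That false positives will certainly double.** This would require the article to fix the uncorrected standard error and the z test, which it does not.
- **That the GEE will cluster on classroom or child and ignore the center.** Simulated clustering on classroom did give 0.11 (ICC 0.02) to 0.16 (ICC 0.05). However, the article names the center as the randomised unit and promises to account for correlation at center level, so this is speculation.

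**Conclusion.** The point holds in conditional form. If logistic GEE is run with clustering on center, an uncorrected robust standard error and a Wald z test, the nominal 5% test of the intervention effect has a true error of about 11–14%, or 2.2 to 2.8 times nominal. In the balanced case its 95% intervals are about three quarters of the correct width. This rests on five centers per arm, which the article states. It also rests on the usual default form of GEE and a 5% level for these tests, which are assumed. Within the ranges tried, the unstated ICC and proportion hardly matter.

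The weight is secondary. The point concerns categorical measures such as the contextual observation codes or weight-status categories, and only if they are compared between arms. It is worth settling before analysis because a better-calibrated test is readily specified, but it does not threaten the primary comparison.

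**What to change.** Add to the analysis plan that, for categorical measures, the GEE clusters on preschool center and uses a small-sample bias-corrected sandwich variance with a t reference on about 8 df (10 centers less 2 arms). Name the correction in advance. In simulation the milder leverage correction gave 4.6–5.8%, and the stronger one gave 2.9–3.5%, which is somewhat conservative. Changing the reference to t8 without correcting the variance is not enough (6.7–8.8%).

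A permutation test over the center allocation is an acceptable alternative. It must follow the actual randomisation, which was stratified by center size and existing activity policy and used the Efron procedure. Unrestricted, there are C(10,5) = 252 splits into five and five. Stratification leaves fewer, so the attainable p-values are coarse and should be checked first.

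The plan should also list which categorical measures will be compared between arms.

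The cost is small: no change to design, data collection or the primary analysis. Intervals become wider, by a factor of about 2.306 / 1.753 = 1.32 in the balanced case, which is the uncertainty that ten centers actually carry.
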